### Data collection

Navigators document completion of STAR workflow processes in the patient’s EHR through the care management electronic documentation form, and then data are exported into a secure, research database (REDCap) [42]. All clinical and outcomes data are collected directly from the AH EHR system and Enterprise Data Warehouse (EDW). Data for study population description are presented in Table 2. Data are collected on a near real-time basis and include physiologic measurements (e.g., mean arterial pressure), laboratory values (complete blood count, basic/comprehensive metabolic panel, lactate), basic sociodemographic characteristics (e.g., age, gender, race, marital status, insurance status), past medical history (e.g., comorbidities, prior healthcare use, medication history), hospital procedures (e.g., mechanical ventilation), and organizational variables (e.g., hospital).

**Table 2 Tab2:** IMPACTS study patient characteristics

Characteristic	Usual care (*n* =)	STAR program (*n* =)
Age at admission (years)		
Median (IQR)	–	–
> 65 years	–	–
Gender		
Male	–	–
Female	–	–
Race		
White	–	–
Black	–	–
Other	–	–
Marital status		
Married	–	–
Separated or divorced	–	–
Single	–	–
Widowed	–	–
Insurance		
Medicare	–	–
Medicaid	–	–
Private	–	–
Self pay/other	–	–
Comorbid conditions		
Chronic lung disease	–	–
Chronic renal disease	–	–
Diabetes	–	–
Heart failure	–	–
Malignancy	–	–
Myocardial infarction	–	–
Peripheral vascular disease	–	–
Charlson Comorbidity Index, median (IQR)	–	–
Number of hospital admissions < 6 months, median (IQR)	–	–
Index hospitalization organ dysfunction measures		
Mean arterial pressure (mmHg), median (IQR)	–	–
Mean arterial pressure < 70 mmHg, *n* (%)	–	–
Creatinine (mg/dl), median (IQR)	–	–
Creatinine > 2.0 mg/dl, *n* (%)	–	–
Bilirubin (mg/dl), median (IQR)	–	–
Bilirubin > 2.0 mg/dl, *n* (%)	–	–
Platelets (cells/μl), median (IQR)	–	–
Platelets < 100 cells/μl, *n* (%)	–	–
Lactate (mmol/L), median (IQR)	–	–
Lactate ≥ 2.0 mmol/L, *n* (%)	–	–
Mechanical ventilation during index hospitalization	–	–
Vasopressor receipt during index hospitalization	–	–

*IMPACTS* Improving Morbidity during Post-Acute Care Transitions for Sepsis, *IQR* interquartile range, *STAR* Sepsis Transition and Recovery

### Study outcomes

The primary outcome is a composite, dichotomous endpoint of all-cause mortality or unplanned hospital readmission assessed 30 days post index hospital discharge (Table 3). This combined outcome is ideally suited to our pragmatic study design because the elements are uniformly captured from data contained in the AH EDW, minimizing non-differential assessment, outcome misclassification, and missing data. Additionally, mortality and hospital readmission are widely regarded as patient-centered outcomes, and rates for both adverse outcomes remain high after sepsis hospitalization [43–45]. Finally, readmission rates have recently declined secondary to focused initiatives [46]. However, some data suggest increased mortality during the same interval [47], indicating the importance of measuring mortality and readmission rates in combination. Mortality is defined as any date of death documented in the AH EDW from index hospital presentation to within 30 days of index hospital discharge, including events from national death record data fed monthly into the EDW [48]. Readmission is defined as any unplanned inpatient or observation encounter to any of 47 AH hospitals within the 30 days following index hospital discharge. Both inpatient and observation status hospitalizations count toward the readmission outcome, because either status represents an adverse event important to patients and healthcare systems. This information is captured from encounter data in the AH EDW and has been previously extracted by the study team.

**Table 3 Tab3:** IMPACTS primary and secondary outcomes

Clinical and cost outcomes	Usual care (*n* =)	STAR program (*n* =)
Primary outcome		
30-day all-cause mortality or hospital readmission	–	–
Secondary outcomes		
30-day all-cause mortality	–	–
30-day hospital readmission	–	–
30-day sepsis/infection-related hospital readmission	–	–
30-day chronic lung disease-related hospital readmission	–	–
30-day heart failure-related hospital readmission	–	–
30-day acute renal failure-related hospital readmission	–	–
30-day emergency department visits	–	–
30-day acute care-free days alive	–	–
30-day acute care costs	–	–
30-day total healthcare costs^a^	–	–
90-day all-cause mortality	–	–
90-day hospital readmission	–	–
90-day sepsis/infection-related hospital readmission	–	–
90-day chronic lung disease-related hospital readmission	–	–
90-day heart failure-related hospital readmission	–	–
90-day acute renal failure-related hospital readmission	–	–
90-day emergency department visits	–	–
90-day acute care-free days alive	–	–
90-day acute care costs	–	–
90-day total healthcare costs^a^	–	–

*IMPACTS* Improving Morbidity during Post-Acute Care Transitions for Sepsis, *STAR* Sepsis Transition and Recovery

^a^Only analyzed among Medicare-insured subgroup

The following secondary outcomes are assessed at 30 and 90 days after hospital discharge: all-cause mortality; all-cause, unplanned hospital readmission; cause-specific hospital readmissions with primary diagnoses (based on *International Classification of Diseases, 10th revision* diagnosis codes) related to sepsis or common infection (i.e., sepsis (A40–41, R65.20–21), pneumonia (J13–18), urinary tract infection (N30, N34, N39.0), skin and soft tissue infection (L00–08)), chronic lung disease (J40–47), heart failure (I50), and acute renal failure (N17); ED visits; acute care costs for services received at ED, inpatient, or observation encounters to any AH facility; total healthcare costs for inpatient and outpatient services received at any AH or outside system hospital or provider clinic (only in the subgroup of patients enrolled in a Medicare Shared Savings Plan with complete claims data tracked in AH EDW); and acute care-free days alive, defined as the sum of days alive without inpatient, observation, or ED encounters (rounded to a full day for any day with acute care utilization) during the interval after discharge. First, the total potential follow-up time is calculated as the number of days from index discharge to the earliest date of death or 30 (or 90) days post discharge (patients who die during their index hospitalization have 0 days alive). Each potential follow-up day is categorized as either an acute care day or an acute care-free day, based on any inpatient, observation, or ED encounter on that day. Total acute care-free days alive are calculated as the total potential follow-up time minus the number of acute care days during the 30 (or 90) days after index hospital discharge.

To provide additional context to understanding STAR implementation, important process measures are tracked in both groups, including: functional assessment or physical therapy consult [49, 50]; mental health assessment by PHQ-2 or PHQ-9 [51]; referrals to physical therapy or outpatient rehabilitation, speech therapy, and behavioral health [52–55]; early outpatient follow-up (i.e., completed outpatient primary care follow-up (or attendance at an AH Transition Services clinic) within 7 days of discharge) [56–60]; and documented medication reconciliation in the EHR during the 30 days post discharge [61, 62]. Because sepsis may occur in the setting of long-standing illness and declining health [63–65], we also measure the quality of end-of-life care, including place of death (i.e., hospital or other location) and the proportion of patients who received a palliative care consult, completed care preferences documentation, and were discharged to a hospice.

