At the initial telephone-based contact with the patient or caregiver during hospitalization, the STAR navigator introduces the STAR program and, in situations when the patient can participate, conducts a mental health screening using the Patient Health Questionnaire (PHQ)-2, with reflex administration of the PHQ-9 for positive PHQ-2 (i.e., ≥ 3 points on a scale of 0–6 points) [34]. The STAR navigator communicates the results to the patient’s attending physician. Additionally, the STAR navigator confirms consultations with physical therapy (with recommendation to consult delivered to the care team, if not in place), antibiotic stewardship (i.e., a coordinated program promoting appropriate antibiotic use with a pharmacist review of type and duration, with a review requested by the navigator if not completed), and an additional infectious disease specialist if ongoing systemic inflammatory response syndrome criteria are present more than 48 h after infection onset (i.e., at least two of the following clinical findings: body temperature < 36 °C or > 38 °C, heart rate > 90 beats/min, respiratory rate > 20 breaths/min, and white blood cell count < 4000/mm^3^ or > 12,000/mm^3^) [35, 36]. Finally, if the patient has a serious, chronic illness and either failure to improve after 5 days or a previous hospital admission in the last 60 days, the STAR navigator recommends a goals of care discussion led by the care team or a palliative care consultation [37]. Every 24–48 h during the remainder of the hospital stay, the STAR navigator reviews the patient’s electronic record, communicates with the patient or caregiver, and checks with the clinical case management team for updated discharge planning. Prior to discharge, the STAR navigator provides infection-specific education to the patient and caregiver, which also includes what to expect during transition from the hospital and written information on scheduled outpatient appointments and planned telephone touchpoints. The STAR navigator also reviews discharge orders and confirms inpatient pharmacist review of high-risk medications, including: appropriate indication if prescribed proton pump inhibitor, opioids, benzodiazapines, or antipsychotics; appropriate medications prescribed for chronic lung disease or chronic heart failure (e.g., inhaled corticosteroids for chronic lung disease; or diuretics, beta blockers, angiotensin-converting enzyme inhibitors, aspirin, or statins for chronic heart failure); and medication doses adjusted as needed if any new or worsening renal failure.

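### Acute care-free days alive start at index discharge although patients are randomised in hospital, so the endpoint cannot see a change in index bed use, and length of stay is treated as a baseline covariate

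*Protocol article*

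**What the plan says.** All references are to the protocol article.

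- **Randomisation and start of STAR.** Study setting and population requires that the patient is still in hospital when the weekday list is generated, so randomisation precedes discharge. Under Trial interventions, the navigator works during the stay: confirming physical therapy and antibiotic stewardship review, prompting infectious disease consultation, recommending goals-of-care or palliative discussions, and every 24 to 48 h reviewing the record. At those reviews the navigator also "checks with the clinical case management team for updated discharge planning".
- **Acute care-free days alive (Study outcomes).** For this endpoint, "the total potential follow-up time is calculated as the number of days from index discharge to the earliest date of death"; the count stops at the 30-day or 90-day limit if that comes first. In addition, "patients who die during their index hospitalization have 0 days alive". The score is that follow-up time "minus the number of acute care days during the 30 (or 90) days after index hospital discharge".
- **Mortality (Study outcomes).** The count takes in "any date of death documented in the AH EDW from index hospital presentation to within 30 days of index hospital discharge". The primary composite is "all-cause mortality or unplanned hospital readmission assessed 30 days post index hospital discharge", and the secondary outcomes are set at 30 and 90 days after discharge.
- **Length of stay.** It is not an outcome in Table 3. Statistical analysis names it, together with discharge disposition, among the baseline covariates whose balance will be assessed.

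**The concern.** Discharge happens after randomisation, and an intervention that works in hospital might move it. Acute care-free days alive are meant to summarise survival and acute care use in one number. As defined, the acute care days between randomisation and discharge are outside the count for anyone discharged alive, while each readmission day costs a full day. If STAR lengthened the stay and cut readmissions, the endpoint would show the gain without the cost. If STAR shortened the stay, it would miss that benefit.

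The plan has no outcome that would pick this up. A difference in stay between arms would appear only in the check of baseline balance, where it would be taken for a chance imbalance instead of a possible effect of treatment. What is at stake is the conclusion about utilisation, not the primary result.

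**Working it through.** **Notation.** Day 0 is randomisation, L the day of index discharge, D the day of death, A the acute care days after discharge and W the horizon (30 or 90).

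**1. The plan's own figure.** The plan gives no figure for this endpoint. Its sample size, used below for scale, reproduces with unpooled variance: (1.96 + 0.84)² × (0.40×0.60 + 0.30×0.70) / 0.10² = 7.849 × 0.45 / 0.01 = 353.2, rounded up to 354 per arm. Nothing below changes it.

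**2. Scoring acute care-free days.**
- Protocol: 0 if D ≤ L; otherwise min(D, L + W) − L − A.
- From randomisation: days alive up to W, minus remaining index days, minus A.

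With no readmission (A = 0):

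| Patient | Clock | L = 4 | L = 10 | L = 20 |
|---|---|---|---|---|
| Survivor, W = 30 | Protocol | 30 | 30 | 30 |
| Survivor, W = 30 | Randomisation | 26 | 20 | 10 |
| Survivor, W = 90 | Protocol | 90 | 90 | 90 |
| Survivor, W = 90 | Randomisation | 86 | 80 | 70 |
| Death on day 25, W = 30 | Protocol | 21 | 15 | 5 |
| Death on day 25, W = 30 | Randomisation | 21 | 15 | 5 |

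For a survivor, L cancels out of the protocol score, so 16 more index days (L = 20 against L = 4) cost nothing. For a death inside both windows the two clocks agree, because a later discharge leaves fewer days before death. The stay therefore enters the protocol score only through deaths.

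**3. Size in an arm mean (illustrative).** A simulation assumed a mean remaining stay of 6.5 days, 13% dead 30 days after randomisation, a 27% 30-day readmission risk and equal hazards in both arms. None of these figures is in the document. Lengthening the stay by 0, 1 and 2 days gave:
- protocol 30-day count: 25.6, 25.5, 25.4, or about 0.1 day lost per extra index day;
- 60-day count from randomisation: 44.1, 43.2, 42.3, or about 0.9 day lost per extra index day.

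The horizons differ, so the levels are not comparable; only the change per extra index day is.

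For scale, the planned 10-point reduction in events, if all were readmissions of an assumed 5 to 8 days, is worth 0.10 × 5 = 0.5 to 0.10 × 8 = 0.8 day. A prevented death would count for more.

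**4. Mortality.** The window runs from presentation to L + 30. A death on day 36 is outside it for L = 4 (closes day 34) and inside it for L = 10 (closes day 40). To size this, assume a constant hazard h = −ln(1 − m)/30, where m is mortality 30 days after randomisation, and a control stay of 7 days after randomisation. With no true effect, a one-day longer stay gives:
- m = 5%: from 6.13% at 37 days to 6.29% at 38 days, +0.16 points;
- m = 10%: from 12.19% to 12.49%, about +0.3 points;
- m = 15%: from 18.16% to 18.61%, about +0.44 points.

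A two-day shift gives about 0.3 to 0.9 points. At 354 per arm and about 14.7% mortality, the standard error of the difference is √(2 × 0.147 × 0.853 / 354) = 0.027, or 2.7 points.

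**The case against.** **The endpoint measures what it says.** Study outcomes defines it over the interval after discharge, which fits the trial's post-discharge aim. That a count including index days falls by about a day per extra index day is nearly true by construction. This stands: the protocol's measure is a legitimate one, and the case is for adding a second count, not replacing the first.

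**No effect on discharge timing is documented.** The cited task can be read as obtaining information from case management, and the other in-hospital tasks are confirmations and recommendations. A reader might infer that STAR moves discharge. The document says neither that nor in which direction, so the concern is conditional.

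**Stay is already compared by arm.** True, so a shift would be visible. But it is labelled a baseline covariate, which invites the wrong reading of any difference.

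**The mortality outcome.** A reader might infer that mortality is counted only from discharge, that in-hospital deaths are lost, or that the discharge clock seriously biases the mortality comparison. The document does not support this. The window opens at presentation, in-hospital deaths count, and a longer stay lengthens the window. A one-day shift produces a small fraction of a standard error.

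**A randomisation clock has its own cost.** STAR continues to 30 days after discharge, so mortality at 30 days from randomisation would stop before the programme ends. With 10 inpatient days remaining, only 20 of the 30 programme days after discharge would be seen. This is a good reason not to redefine secondary mortality.

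**Conclusion.** The point holds for acute care-free days alive and for the labelling of length of stay. For patients discharged alive, index inpatient days after randomisation are never counted as acute care days; this follows from the definition without any assumption. Whether it matters in practice depends on STAR changing the stay, which is plausible but undocumented. Under the stated assumptions, a one-day change in mean stay takes about 0.9 day off a count from randomisation but about 0.1 day off the protocol's 30-day count. The hidden amount is of the same order as the 0.5 to 0.8 day that the design effect would be worth.

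The mortality definition needs no change: about 0.2 to 0.4 points per day of shift, under assumed mortality and stay, is negligible beside a 2.7-point standard error. The primary composite is not undermined, since its readmission component has to start at discharge and its 10-point design effect is far larger than the mortality artefact. This is worth fixing, but it is not fatal.

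**What to change.** 1. Keep the primary composite and all discharge-anchored secondary outcomes as defined.
2. Add a supportive analysis of acute care-free days alive counted from randomisation over a fixed window, for example 90 days, with remaining index inpatient days counted as acute care days. A 90-day window covers the whole STAR programme for any remaining stay up to 90 − 30 = 60 days, and lies within the 90-day post-discharge follow-up already planned.
3. In Statistical analysis, remove length of stay and discharge disposition from the baseline covariates. Report remaining index stay and discharge disposition by arm as post-randomisation outcomes.
4. Optionally, add 90-day mortality from randomisation as a sensitivity analysis.

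This needs no new patients and no new data collection, since it re-cuts dates from the automated allocation and the data warehouse. The cost is a little extra analysis and two versions of one secondary endpoint to present and explain. As the trial is registered and enrolling, the additions should be labelled supportive and fixed before outcomes are compared by arm.

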
After discharge, the STAR navigator follows patients regardless of the discharge location (e.g., home, SNF) and remotely monitors via EHR-based and telephone-based review throughout the 30 days post hospital discharge (Fig. 2). Specifically, the STAR navigator provides telehealth monitoring at < 48 h, 72–96 h, and 7–10 days post discharge. Within 24–48 h of hospital discharge, the STAR navigator contacts the patient or caregiver for initial post-discharge medication reconciliation, with a review by the AH Transition Services pharmacist and confirmation that the patient has filled or received all medications needed. The STAR navigator coordinates with the patient’s primary care provider or AH Transition Services to address any outstanding medication needs. Also at this touchpoint, the STAR navigator monitors for fever (> 38 °C after recheck), new or worsening symptoms (e.g., dyspnea, diarrhea, or redness, swelling, or pain (for skin and soft tissue infection)), and new limitations in functional status (e.g., not out of bed, not eating). Concerns identified through proactive monitoring prompt a primary care provider contact for follow-up within 24 h. If the primary care provider cannot be reached after one attempt, the navigator contacts AH Transition Services to coordinate either a virtual visit with a physician facilitated by community paramedicine or an in-person physician visit [32]. The STAR navigator also meets at least weekly with the AH Transition Services Medical Director to review ongoing cases and coordinate additional support as needed. Additional touchpoints at 72–96 h and 7–10 days post discharge include similar elements (i.e., medication reconciliation, targeted symptom monitoring, vitals and weight checks, confirmation that the patient can make scheduled outpatient appointments) and response (i.e., coordinating follow-up with primary care or AH Transition Services within 24 h for concerning issues). If a provider visit has been completed, the STAR navigator reviews any visit notes, available laboratory values (e.g., complete blood count, basic metabolic panel), and documented therapy plan. After the first 10 days following hospital discharge, the STAR navigator maintains weekly telehealth touchpoints with patients who remain at high risk for poor outcome, defined as any previous positive screen or high-risk comorbid condition (e.g., chronic lung disease, heart failure) [10, 38–40]; and one additional third-week touchpoint with patients considered low risk after the first 10 days post discharge. Each of these post-acute touchpoints include targeted symptom monitoring, vitals and weight check, and escalation to an additional outpatient provider visit within 24 h if there are concerns. Any identified concerns again prompt an attempt to contact the primary care provider followed by AH Transition Services. The STAR program intervention completes 30 days post hospital discharge.

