### Statistical analysis

Primary analyses will follow an intent-to-treat approach such that patients will be analyzed based on the group to which they were initially randomized after exclusion of patients with infection ruled out during their hospitalization. We will assess the balance in the distributions of baseline covariates for patient factors (e.g., age, comorbidities), acuity (e.g., organ dysfunction, mechanical ventilation), length of stay, and discharge disposition (e.g., SNF, rehabilitation, home) between study groups. Comparisons of the two groups will be made using univariate analyses such as the *t* test and chi-square test.

The primary composite outcome, 30-day readmission and mortality, will be compared between the two arms using logistic regression. We will present the effects of the STAR program on the incidence of the composite readmission and mortality outcome as odds ratios and 95% confidence intervals. In addition to the primary intent-to-treat analysis, and since there is significant overlap between general AH Transition Services and the STAR program services integrated within AH Transition Services, we will conduct a modified intent-to-treat analysis excluding usual care patients who attended the AH Transition Services clinic during the 30 days after hospital discharge. Based on historical data, we anticipate an approximately 10% referral rate to AH Transition Services in the usual care group. Finally, we will complete a per-protocol analysis to compare patients in the STAR intervention arm who are eligible at hospital discharge and complete the 30-day STAR program to patients who are eligible at hospital discharge and receive usual care.

Secondary acute care and cost outcomes and process measures will be evaluated using the same approach. We will test different distribution parameters to determine the optimal distribution family for each model and outcome variable (e.g., gamma distribution for costs, Poisson distribution for acute care-free days). Any substantial changes to the study processes will be documented, discussed with investigators at monthly meetings, and incorporated into analyses of study outcomes. All hypothesis tests will be two sided and data will be analyzed using SAS Enterprise Guide v7.1 (Cary, NC, USA).

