### Sample size calculation

This study is designed to detect a 25% relative reduction in the primary outcome, the composite rate of 30-day readmission and mortality, which is reasonable given prior literature suggesting that between 22% and 42% of hospital readmissions after sepsis are preventable, including data from a secondary analysis of the subgroup of sepsis patients in our previous transitions of care trial (relative risk = 0.49, 0.24–0.97) [33]. Based on the historical data, the control group is estimated to have a 40% combined readmission and mortality rate. Group sample sizes of 354 in the STAR group and 354 in the usual care group achieve 80% power (α = 0.05) to detect a 10% absolute reduction between the group proportions (i.e., 25% relative reduction). Under the alternative hypothesis, the proportion in the STAR group is assumed to be 30%.

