### Missing data

We do not anticipate substantial missing data because all outcomes are routinely collected variables and utilization is broadly captured within our large integrated system. Values for patients who do not have healthcare utilization or mortality records during the study follow-up interval are assumed to be null. While utilization may occur outside AH, this is not expected to be a major limitation because of the AH market share and accessibility. Specifically, AH operates three large hospitals in Cabarrus and Mecklenburg Counties and more than 40 hospitals in the region overall. Additionally, any utilization occurring outside the system is anticipated to be non-differentially distributed between groups and thus to impact treatment groups equally. Further, internal historical data indicate that nearly 75% of high-risk patients are Medicare-insured (i.e., Medicare Shared Savings Plan beneficiaries). For these patients, we will have complete healthcare claims within and outside AH facilities during the study interval, as captured through participation in the local AH-managed Accountable Care Organization. We will conduct subgroup analyses within this Medicare-insured population and will use these data to explore missing data patterns that can be adjusted using pattern-mixture methods in sensitivity analyses.

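### The death rule does not exclude deaths learned only through STAR navigator contact, so equal detection of 30-day out-of-hospital deaths in the two arms is not assured

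*Protocol article*

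**What the plan says.** All references are to the Methods of the protocol article.

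- **Study outcomes.** Mortality is "any date of death documented in the AH EDW from index hospital presentation to within 30 days of index hospital discharge". The national death record feed, loaded monthly, is included as one source; no other source is excluded. The composite is justified partly because "the elements are uniformly captured from data contained in the AH EDW".
- **Trial interventions.** The STAR navigator follows patients wherever they are discharged to and "remotely monitors via EHR-based and telephone-based review throughout the 30 days post hospital discharge". Contacts fall within 48 h, at 72–96 h and at 7–10 days. After that they are weekly for patients still at high risk, or a single third-week contact for the others. The caregiver may be the person contacted. Usual care elements are not prescribed and have no such schedule.
- **Data collection.** Navigators document completed workflow steps on a care management form in the health record. On outcomes: "All clinical and outcomes data are collected directly from the AH EHR system and Enterprise Data Warehouse (EDW".
- **Missing data.** "Values for patients who do not have healthcare utilization or mortality records during the study follow-up interval are assumed to be null". The argument that losses are equal between arms is made for utilization outside the system. Deaths are not mentioned in it.

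**The concern.** A shared database gives equal ascertainment only if the routes into it are equal. Here the randomized intervention adds a contact route in one arm, into the record system that supplies outcomes. The rule accepts a death date from any source and reads silence as survival. A death at home, in a nursing facility or in hospice that the national feed does not hold could be found through the navigator in STAR and go unrecorded in usual care. The trial expects deaths outside hospital, since place of death is one of its end-of-life measures.

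Death is a component of the primary composite and a secondary outcome in its own right. With no interim analysis for harm and no monitoring board, the final mortality comparison is in practice the main place where harm would show. Detection that differs by arm would add events to STAR. That would shrink an apparent benefit or resemble an excess of deaths, and a larger sample would not remove it.

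**Working it through.** **1. The plan's own figure.** Inputs from Sample size calculation and Statistical analysis: 40% v 30%, two-sided α = 0.05 ("All hypothesis tests will be two sided"), and "Group sample sizes of 354 in the STAR group and 354 in the usual care group achieve 80% power".

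Unpooled formula: n = (1.960 + 0.842)² × (0.40×0.60 + 0.30×0.70) / 0.10² = 353.2, rounded up to 354. Power at 354 per arm is 80.1% with unpooled variance and 79.8% with pooled variance. The stated size reproduces and is not in question.

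**2. Which deaths can differ by arm.** For the composite, a death matters only if all of these hold:

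- it falls after discharge and by day 30;
- it is not already captured by an AH encounter;
- it does not follow an AH readmission, which already counts as an event;
- it is absent from the national feed when data are extracted;
- in STAR, the navigator learns of it and it reaches the warehouse death field.

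Spurious difference = a × b × c, where a is the share of patients dying outside AH by day 30 without an AH readmission, b is the share of those missed by the feed, and c is the share of the missed deaths recovered in STAR.

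**3. Inputs.** The documents give none of these. The assumed ranges are a = 3–6%, b = 5–20%, c = 80–100%. If navigator-learned deaths never reach the death field, c = 0 and the bias is zero.

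**4. Effect on the composite.** For simplicity the whole difference is taken off the usual care rate, with STAR held at 30%. Power uses z = (p_UC − 0.30) / √{[p_UC(1 − p_UC) + 0.21] / 354}.

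| Case | a × b × c | Points | Patients per 354 | Usual care observed | z | Power |
|---|---|---|---|---|---|---|
| None | 0 | 0 | 0 | 40.00% | 2.805 | 80.1% |
| Low | 0.03×0.05×0.8 | 0.12 | 0.4 | 39.88% | 2.772 | 79.2% |
| Middle | 0.045×0.125×0.9 | 0.51 | 1.8 | 39.49% | 2.666 | 76.0% |
| High | 0.06×0.20×1.0 | 1.20 | 4.2 | 38.80% | 2.475 | 69.7% |

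**5. No true effect, high case.** STAR is observed at 40.0% and usual care at 38.8%, an odds ratio of (0.400/0.600)/(0.388/0.612) = 1.05. The shift is 0.012 / √[(0.2400 + 0.2375)/354] = 0.327 standard errors. The chance of a significant result against STAR rises from 2.5% to 5.1%. The chance of one in its favour falls from 2.5% to 1.1%.

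**6. Mortality alone.** If true 30-day mortality were 12% in both arms (assumed), the high case gives 12.0% v 10.8%, a spurious risk ratio of 1.11.

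**7. The range is not a bound.** If 10 points of the 40% composite were deaths without readmission and 30% of these were missed in usual care only, the difference would be 3.0 points and power about 51%. With equal miss rates in both arms and no true effect, the difference is zero.

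**The case against.** A reader might infer that deaths are in fact ascertained more completely in STAR and that the primary outcome is biased by arm. The documents do not support that. Data collection says only that navigators record completed workflow steps on a care management form. No section says that they enter a date of death, or that the form feeds the warehouse death field.

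Nor does usual care depend on the national feed alone. One definition, one feed and the same AH encounter records serve both arms. Usual care patients may have home health, care management or facility follow-up, and about 10% are expected to be referred to Transition Services. Patients judged low risk after day 10 get only one further STAR contact.

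A monthly feed is a delay and not a loss. With 90-day outcomes planned, extraction after the last patient's day 90 would give that patient's day-30 status about two more monthly loads. The extraction date is operational detail that an article may leave to fuller documents. Contact ends at day 30, so deaths from day 31 to day 90 carry little of this mechanism. Index-stay deaths also count and should be captured alike. Any bias runs against STAR and so would not create a false claim of benefit.

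These points stand, and they reduce the concern to permanent feed misses that a navigator route recovers. They do not remove it. The definition accepts such deaths, and the article asserts uniform capture without an argument that covers deaths.

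There is also a fair objection to one possible remedy. Striking known deaths from the primary count lowers sensitivity in both arms to cure an unproven asymmetry.

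**Conclusion.** The concern holds as a detection bias that the stated rule permits, not as one that has been shown. The claim of uniform capture is not assured for deaths within 30 days, and the non-differential argument does not reach them. The direction is known: extra recorded events in STAR, against a benefit and possibly resembling harm. The size is not known. Under the assumed inputs it is about 0.1 to 1.2 percentage points on both the composite and 30-day mortality, leaving power at 79% to 70%. The low end is negligible, the upper end needs all three inputs at their limits, and zero is possible. This merits a correction to the plan because the guard is cheap. It does not put the design or the sample size in doubt.

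**What to change.** 1. Prespecify an analysis of the primary composite and of 30-day mortality that counts deaths only from sources independent of arm: AH encounters and the national death feed. Apply it identically in both arms, after the feed has caught up with the last patient's follow-up.
2. Report by arm the number of deaths known only from other sources. If there are none, the matter is closed by data.
3. Qualify the statement on uniform capture under Study outcomes: the database is common to both arms, but the routes by which a death reaches it may differ.

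Whether the arm-independent definition is the primary or the sensitivity analysis can be left to the sponsor, provided it is settled before outcomes are compared by arm.

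Cost: a source flag on each death date, which the documents do not show to exist already, and one additional analysis. Whichever analysis uses the narrower definition will omit some genuine deaths, which is why the count in step 2 should be shown beside it.
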